#### Data analysis plan

The primary outcome and all secondary outcomes will be compared between the intervention and standard of care groups in an intention-to-treat population, with all tests two-sided and with the level of significance set at 5%, after the primary outcome has been collected in the last subject. There is no plan for any interim analysis. We will perform exploratory analyses in pre-specified subgroups of patients stratified according to APACHE II, and the length of intervention. We will also perform unadjusted analysis of odds ratio of being functionally independent (defined as ability to walk, use a telephone, self-care, use the toilet and groom) at 6 months after ICU admission in patients in the intervention and standard of care groups. We will perform adjustments on the disease severity (APACHE II score), admission diagnosis, baseline functional status and age. Missing data for primary outcome will be dealt by reporting both worst-case and per-protocol results; no imputation will be used.

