#### Primary outcome

The primary outcome is the physical component of the SF-36 quality of life questionnaire measured in ICU survivors at 6 months. Based on the study by Kayambu et al. [12], where this measure was 60 ± 29 points in the control group, our study is powered to detect a change by 15 points or more, which is within the limits determined as clinically important for patients with COPD, asthma and myocardial infarction [56]. The SF-36 has been validated in the Czech Republic and endorsed by the Institution for Health Information and Statistics (https://www.uzis.cz/en/node/8159).

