### Statistical analyses

#### Sample-size calculation

In studies of critical illness outcome at 6 months using SF-36 scores, the standard deviation varied between 10 and 30 points. In order to have 80% power to detect a 15-point difference in SF-36 scores between control and intervention at the level of significance *p* < 0.05 in the population with a mean of 60 and SD of 30 [12], we would need 108 subjects (54 in each arm). In order to allow for deaths and dropouts, we plan to randomize 150 subjects.

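### The exploratory severity analysis groups APACHE II, a numerical score, into strata; one treatment-by-continuous-score interaction would keep the information that grouping discards

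*Protocol article*

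**What the plan says.** The Data analysis plan of the protocol article gives subgroups one sentence, which announces "exploratory analyses in pre-specified subgroups of patients stratified according to APACHE II" and, as a second stratifier, the length of intervention. The number of APACHE II strata, the cut points and the way the strata will be judged are not stated. Earlier in the same section, the comparison of primary and secondary outcomes is set up "with all tests two-sided and with the level of significance set at 5" percent; whether that level carries over to the subgroups is not stated. A later sentence in the section lists the APACHE II score among the adjustment variables.

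The scale of the trial comes from the Sample-size calculation: "80% power to detect a 15-point difference in SF-36 scores between control and intervention", "in the population with a mean of 60 and SD of 30", for which "we would need 108 subjects (54 in each arm"), with 150 to be randomized to cover deaths and dropouts. That section also notes that in comparable studies "the standard deviation varied between 10 and 30 points".

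**The concern.** The scientific question behind a severity subgroup is whether the benefit of the intervention changes with severity. The Background makes this a natural question, because it describes the sickest patients as being at particular risk of ICU-acquired weakness. Two things make strata a weak tool for answering it.

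- Grouping a numerical score treats patients just either side of a cut as different and patients far apart within a stratum as alike. This costs power to detect a real gradient. The loss comes from the strata themselves, so a between-strata test would not restore it.
- If strata are read one at a time, each holds few patients. A treatment effect that is the same everywhere can then reach significance in one stratum and miss it in another, and be reported as benefit confined to one severity group.

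The first holds for any grouping, with a size that depends on the cut. The second arises only if the strata are judged by separate tests.

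**Working it through.** **Inputs from the article.** Difference 15 points, SD 30, two-sided 5%, 54 evaluable per arm, 150 randomized 1:1, quoted SD range 10 to 30. **Assumptions not in the article.** Two equal strata (27 per arm in each), a separate 5% test in each, and a normally distributed APACHE II score.

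**1. The plan's own sample size.** n per arm = 2 × (1.96 + 0.84)² × (30/15)² = 62.8, so 63 per arm (126 in all; 64 per arm with the t distribution). The stated 54 per arm does not reproduce: it gives 73.8% power at SD 30 (73.1% with t) and would need an SD near 27.8. The source control group is described by "where this measure was 60 ± 29 points in the control group"; SD 29 gives 59 per arm. This is a separate matter and hardly alters what follows, so 54 per arm is kept and 63 and 75 are shown as alternatives.

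**2. Information lost by grouping.** The squared correlation between a normal score and its median split is 2/π = 0.637, so about 64% of the information on a linear interaction is kept.

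- A test with 80% power has expected z = 1.96 + 0.84 = 2.80.
- After the split, z = 2.80 × √0.637 = 2.80 × 0.798 = 2.235.
- Power = Φ(2.235 − 1.96) = Φ(0.275) = 0.61.

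A simulation of 4,000 trials with 54 per arm gave 78% power for the continuous score and 58% for the split.

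**3. Discordant halves under a uniform effect.**

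- Standard error in one half = 30 × √(2/27) = 8.165.
- Power in one half: p = Φ(15/8.165 − 1.96) = Φ(−0.123) = 0.451 (0.438 with t).
- P(exactly one half significant) = 2p(1 − p) = 2 × 0.451 × 0.549 = 0.495 (0.492 with t; 48.1% in the simulation).

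**4. How far this depends on the assumptions.**

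| Uniform effect | SD | Per arm | P(exactly one half significant) |
|---|---|---|---|
| 0 | 30 | 54 | 9.5% |
| 5 | 30 | 54 | 17% |
| 7.5 | 30 | 54 | 25% |
| 10 | 30 | 54 | 35% |
| 15 | 30 | 54 | 49% |
| 20 | 30 | 54 | 44% |
| 15 | 30 | 63 | 50% |
| 15 | 30 | 75 | 49% |
| 15 | 20 | 54 | 34% (35% with t) |
| 15 | 10 | 54 | about 0% |

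At 15 points, SD 30 and 54 per arm, a one-third to two-thirds split gives 52%, and tertiles give mixed significance in 64%.

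**5. The alternative.** Under the same uniform 15-point effect, a single interaction test with the continuous score was falsely positive in 4.7% of simulated trials. A single interaction test between the two halves was falsely positive in 5.2%. The discordance in step 3 therefore comes from reading separate p-values; what grouping itself costs is the power in step 2.

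**6. What the trial can detect at all.**

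- Continuous score: standard error of the slope per SD of APACHE II = 2 × 30/√108 = 5.77, so 80% power needs 2.80 × 5.77 = about 16 points per SD.
- Two halves: standard error of the difference in effects = 8.165 × √2 = 11.55, so 80% power needs 2.80 × 11.55 = about 32 points. Power for a 15-point difference is 25%.

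**The case against.** The strongest reply is that most of the detail above is supplied by the calculation and not by the trial. A reader might infer that the plan uses a median split judged by separate p-values, or that no interaction test is intended. The article supports neither. It is a condensed account, the statistical analysis plan is not shown, and calling the subgroups pre-specified is compatible with cut points and an interaction test being fixed there. Their absence from the article is not a ground for this point.

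A reader might also infer that any uniform effect gives discordant halves about half the time, or that noise alone does so. Neither is right. The 49% needs a real effect of the design size at the top of the quoted SD range; with no effect at all it is 9.5%.

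Nor can it be taken from the article that a suitable model is already planned. The adjustment sentence follows directly on the functional-independence analysis. It does not say that it applies to the SF-36 outcome, or that the score enters as a continuous term.

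Finally, the analysis is labelled exploratory, severity strata are easy to read, and a slope of about 16 points per SD, more than the whole 15-point design effect, is needed for 80% power even with the continuous score.

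All of this stands and limits the point. It does not remove the choice that the article does state, which is to study severity through strata of a numerical score. The information loss would remain even if the unseen plan tests between those strata.

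**Conclusion.** The point holds as a modest improvement to an exploratory analysis. Grouping APACHE II discards information: under a normal score and a linear gradient, a median split keeps about 64%, which turns 80% power into about 61%. The risk of a spurious one-stratum finding is conditional. It is about 49% for two equal halves read by separate 5% tests under a uniform 15-point effect at SD 30 and 54 per arm, and lower for smaller effects or smaller SDs as tabulated. The primary comparison, its significance level and the sample size do not depend on this analysis.

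**What to change.** Make the exploratory severity analysis one treatment-by-APACHE II interaction in the intention-to-treat population, with the score continuous. Report the interaction estimate with its 95% confidence interval, and show predicted treatment effects at, for example, the 25th and 75th percentiles of the score. If strata are still wanted for presentation, show them descriptively and draw no conclusion from within-stratum p-values.

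The cost is about one sentence of analysis wording, with no new data, visits or patients. The downside is an assumed linear effect of severity. The change does not make the trial informative about moderate interactions, for which power stays low, so the confidence interval should carry the message.

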#### Standard care group

Both groups will receive usual best medical and nursing care in the ICU, which includes daily sedation holds when applicable and delirium 12-hourly monitoring (by CAM-ICU scale [58]) and management as usual in the routine practice. Respiratory physiotherapy will also be delivered without alterations. The routine standard care arm will undergo mobilization/rehabilitation delivered by personnel not involved in the study in a usual, routine way. Details of physiotherapy treatment will be recorded but not protocolled in the standard care arm.

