#### Intervention group

In the intervention arm, early goal-directed rehabilitation is protocolled according to the patients’ condition and degree of cooperation (Fig. 3), and there will be pre-defined safety criteria, which are in accordance with current recommendations for active rehabilitation of critically ill ventilated adults [13]. Whilst the safety criteria are binding for the study physiotherapist, the rehabilitation protocol is not and the delivery of physical exercise can be altered according to the actual patient’s condition. However, any alteration and the reason for it will be recorded. The intervention will start as soon as possible and always within 72 h of ICU admission, continuing until ICU discharge. Supine cycling will be delivered as per protocol on a supine cycle ergometer attached to a neuromuscular stimulator. Surface electrodes will be applied to the gluteal, hamstring and quadriceps muscles on both legs. The intensity of muscle stimulation will be delivered at a level able to cause visible contractions (confirmed by palpation if uncertain) in all muscle groups without causing undue pain or discomfort to the participant, according to a regime specified by Parry et al. [44]. Once the patient is more alert, and able to participate, they will be provided with standardized encouragement to engage in therapy. To increase the intervention workload, resistance will be increased incrementally and cycling cadence. If a participant is readmitted to intensive care, the intervention will be re-initiated. The intervention continues until day 28 or ICU discharge, whichever occurs earlier.

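### The missing-data rule for the primary outcome contradicts itself, uses per-protocol for a job it cannot do, and leaves the status of deaths unclear

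*Protocol article*

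**What the plan says.** The Data analysis plan opens with an intention-to-treat comparison: "The primary outcome and all secondary outcomes will be compared between the intervention and standard of care groups in an intention-to-treat population". It closes with the rule for missing primary data: "Missing data for primary outcome will be dealt by reporting both worst-case and per-protocol results; no imputation will be used". It gives no worst-case value and does not say in which arm or direction the worst case applies.

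The Primary outcome section defines the measure as the physical component of the SF-36, "measured in ICU survivors at 6 months". The Sample-size calculation requires 108 evaluable patients and randomises 150, with the difference covering deaths and dropouts together.

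On adherence, the Intervention group section says that safety criteria bind the physiotherapist but "the rehabilitation protocol is not and the delivery of physical exercise can be altered". In the control arm, physiotherapy is "recorded but not protocolled in the standard care arm". Mortality is not in the list of secondary outcomes.

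**The concern.** Three things are wrong or unclear in what the article fixes.

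1. **Worst-case against no imputation.** Both instructions sit in one sentence and cannot both be followed.
2. **Per-protocol as a remedy for missing scores.** An adherent patient without a 6-month score is still without one, and a non-adherent patient with a score is discarded. The method does not address missing data, and it adds selection after randomisation.
3. **Deaths.** Two sections treat them as outside the evaluable set. The Data analysis plan refers to an intention-to-treat population and applies the worst case to missing data without saying whether a death counts as missing.

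What is at stake is the reading of the primary result. The same data can give quite different differences depending on who counts as missing and which value they receive, and the article leaves both choices open.

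**Working it through.** **The plan's own figure.** The loss allowance is (150 − 108)/150 = 42/150 = 28%, or 21 of 75 per arm. It pools deaths and dropouts; the article gives no separate figure for survivors without an SF-36. (The 108 does not itself follow from the stated inputs: 15 points, SD 30, 80% power and two-sided 5% give 63 per arm, or 126, and against 126 the allowance is 24/150 = 16%. That is a separate matter and nothing here depends on it.)

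**The passages side by side.**

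| Section | Deaths are treated as |
|---|---|
| Primary outcome | outside the outcome if in the ICU; unclear if after ICU discharge |
| Sample-size calculation | loss, pooled with dropouts |
| Data analysis plan | not stated: inside an intention-to-treat population, and possibly missing values |

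The first two agree with each other. The third can be squared with them only by choosing a reading that the text does not state.

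**Effect of the worst-case rule.** Inputs from the Sample-size calculation: control mean 60, difference 15 (so intervention mean 75), SD 30, 75 randomised per arm. Assumptions: a 0–100 scale, the same missing fraction m in both arms, and these means and SD in those observed.

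- All missing scored 0 in both arms: 75(1 − m) − 60(1 − m) = 15(1 − m).
- Missing scored against the intervention (0 in intervention, 100 in control): 75(1 − m) − [60(1 − m) + 100m] = 15 − 115m.

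| m | All missing = 0 | Against the intervention |
|---|---|---|
| 5% | +14.25 | +9.25 |
| 10% | +13.5 | +3.5 |
| 15% | +12.75 | −2.25 |
| 28% | +10.8 | −17.2 |

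The against-intervention bound crosses zero at m = 15/115 = 13%.

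**Power if all of the 28% is scored 0.** Variance per arm is 0.72 × 900 + 0.72 × 0.28 × mean². For control this is 648 + 725.8 = 1,373.8 (SD 37.1). For intervention it is 648 + 1,134 = 1,782 (SD 42.2). The standard error is √[(1,373.8 + 1,782)/75] = 6.49, and 10.8/6.49 − 1.96 = −0.30, so power is about 38%. With observed patients only, 54 per arm, the standard error is 30√(2/54) = 5.77, and 15/5.77 − 1.96 = 0.64, so power is about 74%.

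**Why the status of deaths matters.** Suppose there is no effect among survivors (mean 60 in both arms), with 25 control and 17 intervention deaths out of 75 each. The survivor-only difference is 0. If deaths score 0, it is 60 × (58/75) − 60 × (50/75) = 46.4 − 40.0 = 6.4 points, all of it from mortality. The death counts are illustrative, not from the article.

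**The case against.** Several points on the other side carry weight.

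- **A reader might infer that no per-protocol set can be formed.** The documents do not support that. The Intervention group section sets a 72-hour start limit and has every alteration recorded with its reason. Session times are recorded and checked, and control physiotherapy is recorded. A set could be built from these, and its definition may sit in an analysis plan that is not shown. What stands is narrower: per-protocol does not deal with missing outcomes, and this article gives no adherence standard.
- **A reader might take −17.2 points or 38% power as the expected consequence.** Both need every death to count as a missing score. If deaths lie outside the outcome, m covers only survivors without an SF-36, and the article says that telephone collection was chosen to keep that small. The values 0 and 100 are also assumptions.
- **A reader might infer two competing headline results.** The intention-to-treat comparison is named first. Worst-case and per-protocol appear only in the closing sentence on missing data and read most naturally as supplementary. Still, the article does not label them so.
- **A reader might infer that, without a mortality outcome, the result cannot be interpreted.** That goes too far: deaths have to be counted to account for the 150 randomised, and all adverse events go into the electronic case report form. A planned comparison of mortality by arm would nevertheless help in reading a survivor-only score.
- **No imputation may have been meant as no model-based imputation.** That is a fair guess at intent, but it is not what the sentence says.

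Analysing survivors by allocated arm is also often loosely called intention-to-treat. This softens the conflict over deaths but does not say how a death after ICU discharge is handled.

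**Conclusion.** The rule is wrong as written and should be replaced. The contradiction between worst-case and no imputation, and the misuse of per-protocol, are in the stated text and need no calculation. The place of deaths is ambiguous between sections; it is not shown that no rule covers them.

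The numerical consequence depends on m. Under the assumptions above, a true 15-point benefit scored against the intervention is +9.25 at 5% missing and +3.5 at 10%, and it changes sign at about 13%. The figures at 28% are the far end of the range, reached only if all deaths and dropouts are scored as missing. It does not follow that this rule will decide the trial's conclusion. It does follow that the reported worst case, and whether deaths enter it, could be settled after the data are seen.

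**What to change.** Replace the closing missing-data sentence of the Data analysis plan with these provisions, fixed before the arms are compared:

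- **Primary analysis:** patients by allocated arm, SF-36 physical component in those alive at 6 months, described openly as a survivor analysis.
- **Survivors without SF-36:** delete the no-imputation clause; use multiple imputation from baseline and ICU-discharge data, with a tipping-point analysis.
- **Worst-case:** keep only as a labelled sensitivity bound, with the value assigned in each arm stated.
- **Per-protocol:** remove as a missing-data method. If wanted, keep it as a supplementary analysis with its own definition.
- **Deaths:** report 6-month mortality by arm, and add a supplementary analysis of all randomised patients that counts death as the worst outcome. Ranking death lowest is one way among several. The survivor analysis remains primary if the two differ, and both are shown.

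The cost is an amendment to wording and a little extra analysis. Vital status must be recorded at the 6-month contact. The article plans that contact with the patient or family for the SF-36 interview, so obtaining vital status there is a reasonable inference, but it is not a stated item.

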#### Replication of key aspects of trial methods and conduct

The trial is designed to be fully reproducible in an ICU setting in larger, but not necessarily teaching or academic, hospitals, where the FES-CE equipment and trained physiotherapists are available 7 days a week.

The sponsor of the study is a state-governed grant agency that has not had nor will have any role in study design; collection, management, analysis and interpretation of data; writing of the report; or the decision to submit the report for publication.

## Dissemination of results

We will submit the main results of the trial in an open-access peer-reviewed journal within 6 months after the 150th subject has completed the 6-month follow-up visit, which is expected to happen in Q2 of 2020. We will make fully de-identified record-level raw data available in a public database Additional file 2.

## Trial status

This trial is recruiting (recruitment began November 2016, expected finish November 2019) (first patient recruited 4 October 2016, expected end of study 1 July 2020), protocol version 2.0 as of January 2018. For the full WHO Trial Registration Data Set, see Additional file 1.

## Data Availability

All cleaned de-identified raw data will be made available in an open online database (https://data.mendeley.com/datasets) within 6 months of publication of the main results of the trial.

## Abbreviations

D/C: Discharge
FES-CE: Functional electrical stimulation-assisted cycle ergometry
ICU: Intensive care unit
MRC: Medical Research Council
SF-36: 36-Item Short Form Health Survey
